## Methods/design

The project proposed is an open-label, randomised controlled, multicentre clinical trial of children aged 3 months to 2 years of age with epilepsy who have failed to respond to two or more pharmacological treatments (AED or corticosteroids), comparing KD to further AED treatment. The study will be conducted in two phases: first, we will carry out a pilot phase in two centres. If the pilot study recruits successfully, we will proceed to the full trial in a further seven centres. See Additional file 1 for a schematic of the trial design.

Eligible children will be consented via their parents. They will undergo baseline assessment including medical and seizure history, neurological and anthropometric examination, administration of quality of life (Infant and Toddler Quality of Life Questionnaire, [33]) and developmental (Vineland Adaptive Behaviour Questionnaire, [34]) questionnaires and biochemical investigations. They will then start a 2-week observation period with documentation of seizure frequency. If the child is prone to particularly frequent seizures in excess of two per day, then a minimum baseline period of 1 week would be considered sufficient. Food diaries required for diet calculation will be returned by post from all enrolled infants 1 week (or sooner for those with an unstable clinical condition) into the observation period. Standardised seizure records will be kept during the observation period and throughout the trial. Randomisation will be conducted using an Internet randomisation system provided by Sealed Envelope™ (Sealed Envelope Ltd.). Randomisation will occur on day 8 or day 15 for participants to receive the KD or a further AED; the allocated treatment will commence following randomisation, with instruction and training.

The randomisation schedule will be independently generated and held by Sealed Envelope™. Allocations will be released by email to the coordinating centres once the investigator or research nurse has entered eligible participant information into the web-based randomisation service. Participants will be allocated to either the KD or further AED arm using a simple, concealed, randomisation method. Randomisation will aim to achieve 92 in the KD group versus 68 participants in the further AED arm (see calculation in ‘Sample size’ section). An Enrollment Log will be maintained to keep records of the screened and randomised patients at each site. Withdrawn patients will not be replaced and replacement numbers will not be issued. Whilst it will not be possible to blind participants to their treatment allocation, efforts will be made to minimise expectation bias by emphasising in the trial literature that the evidence supporting the KD for seizure control is currently limited.

A second assessment (4 weeks after start of treatment) will include clinical review and a tolerability questionnaire (modified Hague Scale of Side Effects – see Additional file 2). Assessments will be repeated at 8 weeks after the start of treatment including clinical review, administration of the Infant and Toddler Quality of Life Questionnaire, the tolerability questionnaire, and biochemical investigations. After the 8-week assessment, according to patient’s clinical response to treatment with regards seizure outcome and tolerability, the KD (diet group) or AED (standard AED group) will then be continued or changed. Those in the AED group who have failed to achieve seizure control at the 8-week assessment will then be offered the KD outside the context of the trial. Those on the KD who have failed to achieve seizure improvement at the 8-week assessment will continue with medical management, as per clinician decision. All participants will be followed up for 12 months following randomisation for retention, seizure outcome and neurodevelopmental status. See Fig. 1 (Standard Protocol Items: Recommendations for Interventional Trials (SPIRIT) figure: schedule of enrollment, interventions and assessments) and Additional file 3 for the SPIRIT 2013 Checklist (recommended items to address in a clinical trial protocol and related documents).

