**Methods/design:**

An open-label RCT where eligible children (age 3 months to 2 years with epilepsy who have failed two antiepileptic drugs (AEDs)) undergo baseline assessment, including medical and seizure history. Participants then start an observation period (7 or 14 days) with documentation of seizure frequency. Randomisation will occur on day 8 or day 15 to receive the KD or a further AED; the allocated treatment will commence on day 15, with instruction and training. A second assessment (4 weeks after start of treatment) will include a clinical review and tolerability questionnaire (modified Hague Scale of Side Effects – for those allocated to the KD group). Assessments will be repeated at 8 weeks after the start of treatment including biochemical investigations, after which, according to patient response, KD (diet group) or AED (standard AED group) will then be continued or changed. Those in the AED group who have failed to achieve seizure control at the 8-week assessment will then be offered KD outside the context of the trial. Those in the KD arm who fail to achieve seizure control will be changed to standard clinical management. All patients will be followed up for 12 months from randomisation for retention, seizure outcome, quality of life and neurodevelopmental status.

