### Study objectives

The primary objective is to assess the effectiveness of the KD compared to AEDs in the treatment of infants with epilepsy aged 3 months to 2 years of age who continue to have seizures despite previous trials of two AEDs. The secondary objectives are to determine tolerability of the KD relative to standard AEDs, adherence to treatment over time, the effect on quality of life and neurobehavioural progress. Further, we aim to estimate whether the presence of medium-chain fatty acids in the context of use of the KD is associated with seizure control.

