### Discontinuation/withdrawal of participants and ‘stopping rules’

Participants will be withdrawn from the treatment prior to 8 weeks should there be over 50% increase in seizure frequency from baseline or if side effects, such as diarrhoea or constipation, are not resolved by dietary manipulation or medication. Withdrawn patients will not be replaced, but will have scheduled follow-up assessments.

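### The side-effect scale has no described baseline and, per the abstract, no AED-arm scores, so prior symptoms and background-drug effects may be mistaken for diet effects

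*Protocol article*

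**What the plan says.** Methods/design describes the baseline visit as follows: "They will undergo baseline assessment including medical and seizure history, neurological and anthropometric examination, administration of quality of life", then the developmental questionnaire, closing with "questionnaires and biochemical investigations. They will then start a 2-week observation period with documentation of seizure frequency". The side-effect scale is not among the instruments named.

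The scale enters once treatment is under way: "A second assessment (4 weeks after start of treatment) will include clinical review and a tolerability questionnaire". It returns at the next visit: "Assessments will be repeated at 8 weeks after the start of treatment including clinical review, administration of the Infant and Toddler Quality of Life Questionnaire", together with the tolerability questionnaire and bloods. The text names it at no other visit.

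The abstract restricts it to one arm: "tolerability questionnaire (modified Hague Scale of Side Effects – for those allocated to the KD group". The body of Methods/design carries no such restriction.

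Study objectives sets a comparative aim: "The secondary objectives are to determine tolerability of the KD relative to standard AEDs, adherence to treatment over time". Under Outcomes, the matching 8-week secondary outcome is tolerance of the KD, taken from the side-effect questionnaire and blood results. Statistical analysis assigns tolerability to random-effects modelling and, on the natural reading, to the KD group. The legend to Fig. 1 requires baseline procedures to be finished before randomisation.

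**The concern.** A side-effect questionnaire first completed at week 4 records which symptoms are present, not which have arisen since treatment began. These children have already failed two AEDs. The eligibility criteria and the treatment of listed AEDs as trial medicines in either arm imply that many will be on background drugs. Reflux is excluded only when severe; milder reflux, vomiting, constipation and drowsiness at entry are not addressed. The discontinuation section itself gives bowel symptoms as examples, where "side effects, such as diarrhoea or constipation, are not resolved by dietary manipulation or medication", and a child could have had such symptoms before the study.

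Two comparisons could separate prior or drug-related symptoms from effects of the diet: the same child before treatment, or the AED arm at the same visit. The text describes no baseline administration, and the abstract removes the AED arm. What is at stake is the tolerance outcome and the comparative tolerability objective, in a trial whose Background and Discussion stress safety in a very young group.

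**Working it through.** **Step 1. Which instruments have a pre-treatment value in the text** (Methods/design and Outcomes):

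| Measure | Baseline | 4 weeks | 8 weeks |
|---|---|---|---|
| Quality-of-life questionnaire | named | – | named |
| Vineland | named | – | – (12-month outcome) |
| Biochemistry | named | – | named |
| Plasma medium-chain fatty acids | named | – | named |
| Side-effect scale | not named | named | named |

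The side-effect scale is the only one without a stated baseline. The blood-result half of the tolerance outcome does have one.

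**Step 2. Could an unseen schedule already include it at baseline?** Fig. 1 is not available here. But if the scale is reserved for children allocated to the KD, as the abstract says, it cannot be completed at a baseline visit that must be finished before randomisation. The abstract leaves an interval for children randomised on day 8 and starting on day 15, but no form is named in it, and answers then would be given knowing the allocation.

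**Step 3. What each reading allows.**
- KD group only, no baseline: neither a within-child change nor a between-arm contrast.
- Both arms, no baseline: a between-arm contrast, with prior symptoms balanced in expectation; the KD-specific outcome is still a prevalence.
- Both arms with baseline: both comparisons.

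**Step 4. Illustration of size.** The only plan figure needed is the KD group size, which reproduces: 61 per group; 61/0.90 = 67.8, so 68; 1 + (8 − 1) × 0.05 = 1.35; 68 × 1.35 = 91.8, so 92. With the plan's 10% dropout, 92 × 0.90 = 82.8, about 83 KD children assessed.

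Assume a proportion p0 already has a symptom, that it persists, that the form asks about presence, and that the diet newly causes it in a proportion p1 of the others. Then observed = p0 + (1 − p0) × p1. With p1 = 20%:
- p0 = 10%: 0.10 + 0.90 × 0.20 = 28%; pre-existing 82.8 × 0.10 = 8.3 children; share of positives 0.10/0.28 = 36%.
- p0 = 40%: 0.40 + 0.60 × 0.20 = 52%; pre-existing 82.8 × 0.40 = 33.1 children; share of positives 0.40/0.52 = 77%.

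The part due to the diet is 18% and 12% of children respectively. Letting p1 run from 10% to 30% over the same p0 range, the observed figure runs from 19% to 58%.

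**Step 5. How much can still be collected.** Trial status reports 29 randomised; (160 − 29)/160 = 131/160 = 82% of the target could still have a baseline score.

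**The case against.** The strongest reply is that absence at baseline cannot be proved. The list in Methods/design opens with an inclusive word, the visit schedule is in Fig. 1, and the scale is in Additional file 2; neither is available here. That stands as a limit on certainty, and it is why the point is confined to what the text describes. It does not dispose of the point, because the abstract's restriction and the Fig. 1 legend together exclude a baseline-visit score for a KD-only form.

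A reader might infer that every symptom the child already had will be counted as an effect of the diet, and that harm will be overstated several-fold. The documents do not support this. No section says how a reported symptom is attributed. The form may ask only about problems since treatment began, and a scoring rule for new or worsened items could sit in the analysis plan. Any multiple depends entirely on an assumed prevalence.

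Other baseline information exists: history, examination, quality of life and bloods. Adverse events are also reviewed monthly. A clinician may recognise earlier reflux or constipation from these, but they give no earlier score on the same scale.

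If both arms complete the form, randomisation balances prior symptoms in expectation and the between-arm contrast is not biased by the missing baseline. That is correct. A baseline score would then mainly add precision: at assumed correlations of 0.5 to 0.7, adjustment removes r² = 25% to 49% of residual variance. That gain is unavailable to the between-arm comparison if only the KD group is scored, so it supports the proposed design and is not a measure of present harm.

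**Conclusion.** The point holds in limited form. As the text describes it, the side-effect scale is used only at 4 and 8 weeks, is absent from the stated baseline assessment and, by the abstract, goes only to the KD group. On that design the questionnaire half of the tolerance outcome cannot distinguish effects of the diet from prior symptoms or background-drug effects, and it cannot inform tolerability relative to AEDs. The abstract and the body of Methods/design also need reconciling on which arm completes it.

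The size is unknown. The illustrative 28% to 52%, with about 8 to 33 of some 83 KD children carrying a pre-existing symptom, rests on assumed prevalence, persistence and wording of the form. The effect is confined to one component of a secondary outcome; the primary outcome and sample size are untouched. A change is still worth making, because a pre-treatment score cannot be recovered once treatment has started.

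**What to change.** - Methods/design: add the side-effect scale to the baseline assessment, for every child and before randomisation.
- Abstract and Methods/design: reconcile the two so that both arms complete the scale at 4 and 8 weeks, after checking that its items suit children on AEDs. If Fig. 1 already schedules this, correcting the text is enough.
- Outcomes: report items that are new or worse since baseline, and state the comparison with the AED arm that the objective calls for.
- Statistical analysis: enter the baseline score in the random-effects tolerability model, with randomised group as a fixed effect.
- Children already randomised (29 at the time of writing) will lack a baseline. Report change from baseline in those who have one, with all available on-treatment scores as a sensitivity analysis. If the KD-only reading has been followed, earlier AED children may also lack on-treatment scores, so the between-arm comparison should use children randomised after the change.

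The cost is one extra short parent form at visits that already take place, its use in the AED arm, and a minor amendment.

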**Fig. 1 Fig1:**
[figure not shown]
Standard Protocol Items: Recommendations for Interventional Trials (SPIRIT) figure; schedule of enrollment, interventions and assessments. *At baseline, all procedures should be done before randomisation. **Ketogenic diet group only. (X) – As indicated/appropriate. ^1^Complete physical includes weight, length, head circumference, general examination. ^2^Tests to be done: haematology – full blood count (FBC); biochemistry – liver function tests, renal function tests, calcium, urate, glucose, phosphate, vitamin D, selenium, zinc, cholesterol, carnitine profile and beta-hydroxybutyrate; urinalysis – organic acids, urine calcium and creatinine ratio. Results must be received prior to randomisation. ^3^Home monitoring urine dipstick and blood spot ketones done twice a day and recorded in Seizure Diary (only KD arm). ^4^Special assay or procedure – blood sample to be analysed by [name] at ICH

At each of the centres, the paediatric neurologist will work with a dietitian for KD implementation. Treatment will be in accordance with the KD Intervention Manual, which will be agreed with reference to a standard text [35] and discussed with the project management team at the outset during the initial workshop to enable standardisation of treatment between different centres. There will be an AED consensus flowchart (Additional file 4) for guidance regarding management of the participant’s epilepsy, written following an initial workshop with paediatric neurologists from all nine centres; this flowchart will be used to create a standardised manual (AED Consensus Document).

### Selection of participants

Children aged 3 months to 2 years with an established diagnosis of epilepsy, who continue to have epileptic seizures despite treatment with two AEDs, will be screened for entry into the trial. Recruitment will be from hospital-based paediatric neurology centres, with the additional involvement of a user group, Matthew’s Friends Charity, an organisation set up to raise awareness and availability of the KD in the UK, and which now also supports clinics implementing the KD. Many, if not all of the suitable patients will already be under the care of tertiary paediatric neurology centres according to National Guidelines (https://www.nice.org.uk/guidance/cg137).

#### Inclusion criteria

Age between 3 months and 24 months of age (not beyond second birthday at baseline)Diagnosis of epilepsy confirmedSeizure frequency greater than or equal to four seizures/week on average in the baseline periodFailed response to previous trial of two antiepileptic drugs. In the case of infantile spasms, this could include a trial of corticosteroidsChildren with written informed consent from a parent/guardian

#### Exclusion criteria

Continues on corticosteroids less than 2 weeks prior to randomisationMetabolic disease contraindicating use of the KD, e.g. pyruvate carboxylase deficiency, medium-chain acyl-CoA dehydrogenase (MCAD) deficiency from previous medical investigation and screening at baselineProgressive neurological diseaseSevere gastroesophageal refluxPrevious treatment with the KDConcurrent participation in another clinical trial of an investigational medicinal product (IMP)Patients who are prescribed AEDs not listed in the trial IMPsPatients who have a listed contraindication as per the Summary of Product Characteristics (SmPC) to any of the AEDs listed in the trial IMPs

### Sample size

For the primary outcome variable, based on data from Neal et al., [17], we used mean percentage change in seizures from baseline of 62% (SD 45) in the KD group, assuming a change of 90% in the control group (SD 50) (100 = no change in frequency of seizures from baseline) at 90% power and 5% significance. This gives a sample size of 61 in each group (122 in total). Accounting for a 10% dropout rate, gives 68 in each group (136 in total), and inflation for a therapist effect (dietitian) to one group, assuming nine centres, with an average cluster size of eight and an intracluster correlation coefficient (ICC) of 0.05, the inflation factor is 1.35, giving 92 in the KD group and 68 in the control group (160 in total). If dropout was 20%, this sample size would still have 86% power.

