### Statistical analysis

Analysis will be done by intention-to-treat. Baseline characteristics of participants in the control and intervention arms will be summarised. The primary outcome will be seizure count in the final 2 weeks of the intervention period and in the baseline assessment period. Data will be analysed using a Poisson mixed model to account for clustering by centre (synonymous with therapist). The randomised allocation will be entered into the model as a fixed effect as will an indicator of time point (baseline or end of study), whilst the centre will be included as a random effect. Analysis of secondary outcomes (those seizure free and responders) will be analysed using random-effects logistic models – centre being the random effects and randomised group a fixed effect. The process outcomes relating to tolerability and medium-chain fatty acids in the KD group will be analysed using random-effects modelling. Therapist effects will be investigated further in supportive analyses [7, 37].

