### Outcomes

The primary outcome will be the number of seizures experienced during weeks 6–8 compared to the number of seizures in the baseline period.

Secondary outcomes will include (at 8 weeks):Number of children seizure freeResponder rate, defined as the number showing more than a 50% improvement in seizure frequency compared to baseline (taken as the mean daily seizure frequency over the observation baseline period immediately preceding the 8-week review)Tolerance to KD as assessed by side effect questionnaire and blood resultsRelationship between medium-chain fatty acids and seizure control

Secondary outcomes will also include (at 12 months):Retention on treatment (the number of participants who remain on the KD, or the prescribed AED, at 12 months)Quality of life (as measured by the Infant Toddler Quality of Life Questionnaire)Neurodevelopmental outcome (as measured by the Vineland Adaptive Behaviour Scales)

Plasma profiles of medium-chain fatty acids will be evaluated at baseline and at 8 weeks. Assessment of mitochondrial function (respiratory-chain enzymes) and enrichment (citrate synthase) will be determined in white cells and platelets. The effect of specific ratios of medium-chain fatty acids, to mimic patient plasma profiles, upon neuronal mitochondrial function/enrichment (biochemical plus electron microscopy studies) will be documented. Additionally, such fatty acid profiles will be studied, with regards to antiepileptic effect, in an established in vitro (hippocampal slice) model.

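### The stated 90% and 86% power belong to a comparison of mean per-child percentages of baseline, not to the Poisson count model named as the primary analysis

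*Protocol article*

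**What the plan says.** In the protocol article, Sample size, the calculation is introduced as being for the primary outcome variable. The treated arm enters as "we used mean percentage change in seizures from baseline of 62% (SD 45) in the KD group" and the control arm as "assuming a change of 90% in the control group (SD 50) (100 = no change in frequency of seizures from baseline"). The target is set "at 90% power and 5% significance", and the result is "This gives a sample size of 61 in each group (122 in total"). Dropout comes next: "Accounting for a 10% dropout rate, gives 68 in each group (136 in total"). A therapist effect is then applied to the diet arm only, "with an average cluster size of eight and an intracluster correlation coefficient (ICC) of 0.05, the inflation factor is 1.35", which leads to 92 and 68. The section adds that power would still be 86% if dropout were 20%. Background describes the source quantity, in the earlier trial in older children, as a mean percentage of baseline seizures.

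Statistical analysis defines the endpoint differently: "The primary outcome will be seizure count in the final 2 weeks of the intervention period and in the baseline assessment period". It specifies a Poisson mixed model with allocation and time point as fixed effects and centre as the random effect. Outcomes agrees with that section: "The primary outcome will be the number of seizures experienced" in weeks 6–8, set against the number in the baseline period. The percentage scale returns only in dichotomised form, as the secondary responder rate.

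**The concern.** A mean of per-child percentages gives each child one vote, and the SDs of 45 and 50 are spreads between children. A Poisson model with centre as its only random effect has no term for differences between children. Its estimating equations match observed to fitted totals of counts, so a child with ten times the seizures has about ten times the influence on the treatment contrast.

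The eligibility rule allows this to matter. Inclusion criteria set a floor of 4 seizures a week and no ceiling. Methods/design provides a shorter baseline for children with more than two a day. Such a child, at 14 a week, already carries 14/4 = 3.5 times the weight of one at the floor. Discussion says that many syndromes at this age have frequent seizures.

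At stake is whether the trial has the power it claims for the analysis it names, and whether its main estimate describes the typical child or mostly the few with the highest counts.

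**Working it through.** **1. The plan's own figures (all inputs from Sample size).** Difference 90 − 62 = 28; SDs 45 and 50; two-sided 5%; 90% power.

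- n per group = (1.960 + 1.2816)² × (45² + 50²) / 28² = 10.507 × 4525 / 784 = 60.6, so 61.
- Dropout: 61 / 0.9 = 67.8, so 68.
- Design effect: 1 + (8 − 1) × 0.05 = 1.35. Then 68 × 1.35 = 91.8, so 92. Total 92 + 68 = 160.
- Power at 20% dropout: effective sizes 92 × 0.8 / 1.35 = 54.5 and 68 × 0.8 = 54.4. SE = √(2025/54.5 + 2500/54.4) = 9.12. 28/9.12 − 1.96 = 1.11, giving 86.7% (86.1% with the t distribution).

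Every figure reproduces as a test of two mean percentages. The article gives no event rate, rate ratio or dispersion from which power for a count model could follow.

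**2. The same effect on the count-ratio scale.** The ratio is 62/90 = 0.689, with log −0.3727 (squared, 0.1389). Relative variances are (45/62)² = 0.527 and (50/90)² = 0.309, summing to 0.835. With the child as the unit of variance, count weighting multiplies the variance by 1 + CV², where CV is the coefficient of variation of baseline counts between children. CV is an assumption.

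n per group = 10.507 × 0.835 × (1 + CV²) / 0.1389 = 63.2 × (1 + CV²)

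| Assumed CV | Evaluable n per group for 90% | Power of 92/68, 10% dropout | Power, 20% dropout |
|---|---|---|---|
| 0 | 64 | 89% | 85% |
| 0.5 | 80 | 82% | 77% |
| 1.0 | 127 | 62% | 57% |
| 1.5 | 206 | 43% | 39% |
| 2.0 | 317 | 30% | 27% |

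Only when all children have nearly the same baseline count do the stated figures carry over.

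**3. Simulation.** 61 analysed per arm; each child's end-to-baseline ratio gamma distributed with the article's means and SDs; 14-day windows. Assumed: lognormal baseline rate, median 5 a day, cut off below 4 a week. The three analyses were:

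- a test of mean per-child percentages;
- a count-weighted ratio of end to baseline counts, with a child-level robust SE;
- a Poisson model in which the change also varies randomly between children.

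| Baseline log-SD (assumed) | Per-child percentage | Count-weighted | Poisson with random change |
|---|---|---|---|
| 0.5 | 85% | 79% | 95% |
| 0.8 | 85% | 68% | 96% |
| 1.0 | 84% | 61% | 93% |
| 1.3 | 84% | 53% | 94% |
| 1.5 | 83% | 50% | 96% |

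Repeat runs of the count-weighted column gave 78–81% at log-SD 0.5 and 48–50% at 1.5. The percentage column sits a little under 90% because Poisson counting noise is added to the assumed SDs. At log-SD 1.3 the six highest-frequency children of 61 hold about 47% of an arm's baseline seizures, and the estimated count ratio has a 95% range of about 0.44 to 1.10. The random-change model rejected a true null in 4.2% of 500 runs at log-SD 1.3.

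**4. Limits of these numbers.** The formula in step 2 falls faster than the simulation at wide spread. Part of the reason is that the robust test is somewhat liberal there: in a companion run with a mean of 100 seizures and CV 2 it rejected a true null in 9.5% of runs. The simulated power at the wide end is therefore, if anything, generous. The companion run also shows why power from model-based Poisson SEs means nothing here: at CV 1, with no child-level or overdispersion term, a true null was rejected in about 72% of runs. Steps 2 and 3 read the treatment effect as the difference between arms in change from baseline; whether the listed fixed effects deliver that is a separate matter.

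**The case against.** The strongest reply is that counts as such are not the fault. A Poisson mixed model that lets the change vary between children weights them nearly equally, and in the table above it keeps 93% to 96% power at every assumed spread. A negative binomial model of end counts with baseline rate as covariate also moves towards equal weights. Sizing on a published summary and analysing with a richer model is ordinary practice, and fuller model detail may sit in the full protocol or analysis plan, which are not shown.

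Most of this stands. It confines the point to the model the article specifies, in which centre is the only random effect, and it means the loss would disappear under some child-level corrections. A random child intercept alone would not be enough, since it leaves the count weighting in place. The reply does not remove the mismatch. The article does more than omit detail: it states a percentage in one section and a count in two others, and no later model specification makes the first section's power apply to the model written here.

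It is also fair that the simulated contrast stands in for the mixed model rather than fitting it, and that baseline spread and the gamma shape are assumptions.

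**Conclusion.** The point holds in this form: 90% and 86% are the power of a comparison of mean per-child percentages, and they are not shown to be the power of the Poisson mixed model as written. The mismatch follows from the text alone. Its size does not. Under assumed baseline log-SDs of 0.5 to 1.5, count weighting with a robust SE gives roughly 80% to 50%, and near-equal baselines would give almost no loss.

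Some stronger readings are tempting but unsupported:

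- A reader might infer that the trial has about 50% power. The document gives no baseline distribution, so no single figure can be fixed.
- A reader might infer that the two measures could point in opposite directions. The simulations draw each child's ratio independently of baseline, so both target 0.62/0.90 = 0.69; a reversal would need an effect that varies with baseline frequency, and nothing in the document shows one.
- A reader might infer that the endpoint is an arm's total seizures. The article speaks only of a count or number of seizures; the dominance of high counts comes from the model's weighting.
- A reader might infer that the sample size arithmetic is wrong. It is not.

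**What to change.** Use one definition in Sample size, Statistical analysis and Outcomes.

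- **Preferred:** make the primary analysis each child's daily seizure rate at the end of the intervention relative to that child's own baseline daily rate, with children weighted about equally. Options are the percentage of baseline as sized, its log-ratio, a negative binomial model with log baseline rate as covariate, or a Poisson mixed model with a child-level random change. Say in one sentence how the 62 and 90 relate to the chosen estimate. A count-weighted ratio can be reported as supportive.
- **Alternative:** keep the count model as written, and replace 90% and 86% with its power under a stated rate ratio, baseline spread and overdispersion.

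The cost is wording and a short recalculation; the second route may give a less favourable stated power. No new patients or data are needed. Trial status reports 29 of the planned 160 randomised, so the change can still be made, and it should be fixed before anyone choosing the analysis sees comparative data.
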